### Trial design

TURRIFIC is a multicentre randomised open label controlled study to evaluate whether rifampicin is superior to UDCA in the reduction of pruritus in parallel groups of women with severe ICP presenting between 14^+ 0^ and 33^+ 6^ weeks gestation. Initial random allocation to treatment with rifampicin or UDCA is in a ratio of 1:1.

### Trial setting

The study is being conducted in11 academic hospital centres across Australia and internationally in the UK, Sweden, Finland and The Netherlands. [See list at www.adelaide.edu.au/TURRIFIC].

### Participants

Potentially eligible participants are identified via antenatal clinics, antenatal assessment units and antenatal wards and by review of laboratory BA results.

Women attending for management of severe early onset ICP are invited by the treating physician/obstetrician to consider participation in the study, and if agreeable, provide written informed consent to participate.

### Inclusion criteria

Women are considered eligible for inclusion into the trial with the following criteria:
Severe ICP (defined as pruritus with increased total serum BA ≥40 μmol/L) confirmedViable pregnancy between 14^+ 0^ and 33^+ 6^ weeks gestation inclusive (as determined by ultrasound pregnancy dating)No known lethal fetal anomalySingleton pregnancyObstetric care in a consultant-led unitAged 18 years or overWritten informed consent has been obtained

Standardisation of serum BA concentration measurements: participating units will have tested a series of serum samples sent out from Adelaide, for comparison and correlation with the Adelaide values, and subsequent adjustment of the results from the local laboratories to enable standardisation of the results across the trial. Similar quality control testing will be carried out every 12 months.

Women who present with non-severe ICP (total serum BA < 40 μmol/L) between 14^+ 0^ and 33^+ 6^ weeks gestation, and who then progress, with or without UDCA treatment, to severe ICP (total serum BA ≥40 μmol/L) prior to 34^+ 0^ weeks gestation, are eligible for entry into the trial, providing they are willing to accept random allocation to treatment (with a wash-out period of any pre-existing UDCA treatment for 4–7 days to enable baseline biochemical data to be obtained, and confirm eligibility only if serum BA were measured ≥40 μmol/L while not taking UDCA), they meet the other inclusion criteria and they do not meet any of the exclusion criteria (below), in which case they will be randomised either to rifampicin therapy or to commence/continue with UDCA therapy.

### Exclusion criteria

A potential participant who meets any of the following criteria will be excluded from participation in this study:
A decision has already been made for delivery within the next 48 hThere is allergy to any component of the UDCA or rifampicin tabletsThe woman is taking other medication that has a significant interaction with rifampicin treatment, including saquinavir and ritonavir in combination for treatment of HIV, daclatasvir, simeprevir, sofosbuvir and/or telaprevir for treatment of hepatitis C, isoniazid and/or pyrazinamide for treatment of tuberculosisGeneral anaesthesia within the previous 3 months to avoid the risk of inadvertent and unrecognised previous halothane exposureThere is a multi-fetal gestationThere is laboratory-confirmed active hepatitis A or hepatitis B, or positive serology for hepatitis CThere is current pre-eclampsia (ISSHP criteria) [30]There is a known active primary hepatic disorder, including α-1-antitrypsin deficiency and autoimmune hepatitis, including primary biliary cholangitisThe woman is currently taking medication, which causes deranged liver enzyme valuesThe woman is unwilling for her baby to have standard vitamin K administration at birthThe woman has previously participated in TURRIFIC

A woman will not be excluded, and may be randomised, if she is known to have:
A known genetic disorder associated with cholestasisAsymptomatic cholelithiasis (no colicky right upper quadrant pain/jaundice)Current gestational diabetes (GDM) (WHO criteria) [31]

## Interventions

The intervention under test is rifampicin (rifampicin) tablets 300 mg twice daily and the comparator treatment is ursodeoxycholic acid (UDCA) tablets up to 2000 mg daily, prescribed as per the usual local protocols.

Women meeting the inclusion criteria and consenting to participation will be randomly allocated to treatment with rifampicin or UDCA at study entry. The duration of treatment will range from 1 day to a maximum of 28 weeks, for a participant randomised at 14 weeks who does not deliver until 42 weeks.

Within the trial, both UDCA and rifampicin are usually dispensed by the local hospital pharmacy.

### Ursodeoxycholic Acid (UDCA)

There are no known drug contraindications to UDCA.

The starting dose of UDCA is 450-1000 mg daily (450 mg or 500 mg tablets as per local pharmacy stock to be taken once daily or twice daily), increased in increments of 500 mg per day every 3–14 days, if there is no biochemical/clinical improvement, up to a maximum of 2000 mg per day [32]. UDCA will be continued until birth and then discontinued, or it may be weaned at the discretion of the treating clinician.

### Possible side-effects

Common side effects include soft loose stools or diarrhoea.

Less common side-effects include urticaria.

### Rifampicin

The dose of rifampicin is 300 mg twice daily. Administration of rifampicin will be withheld if, during treatment, there is a rise of serum ALT above 200 U/L, and the management of such patients discussed with senior clinicians, including CI [name] and/or CI [name], to decide about continuation of rifampicin therapy. Rifampicin will be weaned after birth by 150 mg every 3 days.

### Possible side-effects

Commonly, body fluids, including urine, stools, saliva, sputum, sweat and tears, turn red-orange.

Other side effects from rifampicin are not common, but can include headache, muscle pain, bone pain, heartburn, upset stomach, vomiting, stomach cramps, chills, diarrhoea, urticaria, sores on skin or in the mouth, fever, or jaundice.

### Drug interactions

Halothane, listed in the Product Information as an exclusion for rifampicin treatment, is not currently used in the countries where the trial is being conducted. It is possible that immigrant women may have been exposed to halothane before arrival. All women being screened for eligibility will be asked if they have had a general anaesthetic within the previous 3 months and, if so, they will be excluded from the trial to avoid the risk of inadvertent and unrecognised previous halothane exposure. It is most unlikely that women with active or currently treated tuberculosis (TB) will be recruited to the trial, but women taking isoniazid or pyrazinamide will not be considered for inclusion.

Rifampicin can have significant interaction with other drug therapies. In particular, it can interact with hormonal contraceptive agents and appropriate advice will be given in the postpartum period for those women who have been taking rifampicin to take different or additional contraceptive precautions for a month after ceasing rifampicin therapy.

### Current practice

Women who present with mild to moderate ICP remote from term will usually be offered treatment with UDCA, with ongoing surveillance in the obstetric and obstetric medical clinics, and consideration given to delivery between 38 and 40 weeks gestation.

Women who present with, or who progress to, severe ICP will usually be offered treatment with increasing doses of UDCA, with the addition of rifampicin, if considered necessary, to reduce the serum BA concentrations, even though this is not a standard indication. Delivery will often be brought forward to between 36 and 37 weeks gestation, especially if there is subjective reduction in fetal movements.

### Adherence to and returns of study treatment

Treatment adherence will be measured by review of the medication dosing card and participant self-report at each visit. Medication dosing cards will be collected when they are completed and at the end of the study.

There is no compulsion to return any unused medication. However, study staff will offer to dispose safely of any unused medications that the participant wishes to relinquish.

### Concomitant medication

All prescribed and “over the counter” medications deemed necessary by an attending healthcare professional to provide adequate supportive care to the woman are permitted during the trial. All medications taken by the woman, including vitamin K and other supplements, are to be recorded in the participant’s eCRF.

Women taking rifampicin and who are subsequently commenced on medications known to have significant interaction with rifampicin will be withdrawn from the trial.

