**Table 1 Tab1:**
[figure not shown]
Trial Timeline

*GA* gestational age, *ALT* alanine transaminase, *LFTs* liver chemistry analysis, *INR/APTT* International Normalised Ratio/Activated Partial Thromboplastin Time

Notes to Table 1

^1^All screening assessments are part of normal clinical practice

^2^Bile acid samples need to be drawn shortly before a scheduled dose of UDCA, though fasting is not required. Women previously prescribed UDCA for treatment of mild ICP, and agreeing to randomisation, will have basal assessments performed 4–7 days after ceasing such therapy prior to randomisation into the trial

^3^Study treatment started after randomisation. Dose to be adjusted by PI if indicated by symptoms and/or blood tests taken during normal clinical practice

^4^Adverse events will be recorded from study entry until post-delivery discharge of woman and baby. All SAEs are to be reported to the Coordinating Centre within 24 h of Investigator knowledge

Women eligible for the trial, whether or not they participate, will be asked about their willingness to take part in a subsequent trial of planned delivery of such affected women at 36^+ 0^ weeks gestation compared with expectant management in terms of neonatal outcomes.

Women taking part in the study will be asked about any other drugs that have been prescribed or initiated after randomisation. If such medications include agents known to have a significant interaction with rifampicin, then a woman taking rifampicin will be asked to withdraw from the study, although any data obtained until withdrawal will be included, and any pregnancy outcome data will be recorded (with her consent).

Participating women will also be asked at recruitment about any antibiotics they may have taken in the 3 months prior to recruitment, as well as any progesterone supplements they may have taken.

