### Withdrawal of participants

It will be made clear to participants that they remain free to withdraw from the clinical trial at any time without the need to provide any reason or explanation; and that this decision will not impact on any aspect of their ongoing clinical care. The investigator will be able to discontinue participants from either of the study drugs in the event that they judge that alternative treatment is required, without the woman being necessarily withdrawn from the study. Participants will not be withdrawn for self-reported low or non-adherence to their study treatment.

Permission will be sought to complete and use data up to the point of withdrawal including both:
trial specific datadata collected as per routine clinical practice

Permission will also be sought to ascertain and record subsequent perinatal outcome data.

The reason for withdrawal will be recorded in the eCRF, and, if it was due to an Adverse Event, the investigator will follow up to resolution/stability.

Similarly, it will also be made clear to participants that they remain free to withdraw from any future sub-studies to which they have agreed at any time without the need to provide any reason or explanation; and that such a decision will not impact on any aspect of their ongoing clinical care.

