### Data analysis

A detailed Statistical Analysis Plan will be developed by the trial statistician (who is independent of the Sponsor) and agreed by the Trial Management Committee (TMC) before the analysis is undertaken. The analysis and presentation of results will follow the most up-to-date recommendations of the CONSORT group. Analyses will be completed in STATA® version 13.0 or later.

All analyses will follow the intention to treat principle, i.e. data from all randomised woman and babies will be analysed according to the treatment they were allocated to irrespective of the treatment they received or whether they received any treatment at all.

Blinding will not be possible for participants and care providers, because of the open nature of the interventions, nor will the DSMC be blinded to allocation in their assessment of outcomes and safety, but the outcome data will be blinded to the data analysts by concealing the group allocation prior to the analysis.

Demographic and clinical data will be summarised with counts and percentages for categorical variables, means (standard deviations) for normally distributed continuous variables and medians (with interquartile or simple ranges) for other continuous variables.

For the primary outcome, the effectiveness of the interventions will be assessed by calculating the differences in mean pruritus score with 95% confidence intervals (CI), determined with a linear regression model, using Generalised Estimating Equations (GEEs).

All comparative analyses will be performed adjusting for stratification variables and baseline measures of the outcome, where relevant. Binary outcomes will be analysed using log binomial regression models. Results will be presented as adjusted risk ratios plus 95% CIs. If the model is unstable, log Poisson regression models with robust variance estimation will be used [34]. Continuous outcomes will be analysed using linear regression models, and results will be presented as adjusted differences in means (with 95% CIs). Analysis of outcomes that are measured repeatedly over time (severity of pruritus and biochemical markers) will use repeated measures analysis techniques, including GEEs and/or random effects.

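### Starting an interacting drug while on rifampicin ends trial follow-up, so later itch scores are not collected and missing data can depend on arm

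*Protocol article*

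**What the plan says.** Concomitant medication (under Interventions) states that women on rifampicin who are "subsequently commenced on medications known to have significant interaction with rifampicin will be withdrawn from the trial". The Notes to Table 1 cover the same event in softer words: "a woman taking rifampicin will be asked to withdraw from the study, although any data obtained until withdrawal will be included". They add that pregnancy outcome data will be recorded afterwards if she consents. Neither place gives a matching rule for a woman taking only UDCA.

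Withdrawal of participants lets the investigator discontinue either study drug when alternative treatment is judged necessary, "without the woman being necessarily withdrawn from the study". It also says that low adherence is not a reason for withdrawal. For women who do leave, it covers data up to withdrawal and then says: "Permission will also be sought to ascertain and record subsequent perinatal outcome data".

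Data analysis adopts intention to treat: "data from all randomised woman and babies will be analysed according to the treatment they were allocated to", whatever treatment they received. The primary outcome is the itch score on a visual analogue scale, due at 1 week, then monthly to 28 weeks, then weekly to delivery. The primary analysis is a linear model fitted by GEE. Dealing with missing data mentions only loss to follow-up, expects little of it, and plans multiple imputation in a sensitivity analysis.

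**The concern.** The rule turns a drug-interaction event into an end of follow-up for the primary outcome. The event happens after randomisation, and who is exposed to it depends largely on allocation. A woman on UDCA alone who starts the same medication stays in and goes on contributing scores; a woman on rifampicin does not.

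Unequal numbers of missing scores do not by themselves bias the comparison. Bias arises if the women who leave would have gone on to have different itch from those who stay, beyond what the model's covariates explain. That is possible, because new medication may accompany a change in health. Standard unweighted GEE gives no general protection here. Imputation would rest on an assumption that the data cannot check, because the scores needed to check it were never taken. An analysis plan written later cannot recover them.

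**Working it through.** **1. The passages side by side**

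| Question | Concomitant medication | Notes to Table 1 | Withdrawal of participants | Data analysis |
|---|---|---|---|---|
| Does she leave the study? | Yes, automatically | She is asked to | Not necessarily, when a drug is stopped | Not addressed |
| Scores before leaving | Not addressed | Kept | Kept, with permission | Analysed as allocated |
| Itch scores after leaving | Not addressed | Not provided for | Not provided for | Wanted for all randomised women |
| Other outcomes after leaving | Not addressed | Pregnancy outcome, with consent | Perinatal outcome, with permission | Analysed as allocated |

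Two mismatches follow. The first is mandatory withdrawal against a request to withdraw. The second is leaving the trial for this one reason, while other reasons for stopping a study drug need not end participation. Safety reporting is said to run to 6 weeks after delivery, but adverse-event follow-up after withdrawal is stated only where an adverse event caused the withdrawal.

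**2. Who is covered**

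The trigger is taking rifampicin. That covers the rifampicin arm while on the drug. It covers UDCA-arm women only once rifampicin is added, which Subsequent visits allows when maximal doses are reached. The losses therefore fall mainly, but not solely, on one arm.

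**3. Power**

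The article gives no figure for these withdrawals. Its nearest relevant figure is about 75% power with 54 per group, a 14 mm difference (−16 against −30 mm), an SD of about 28 mm and two-sided 5%.

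Reproduced: z = 14 / (28 × √(1/54 + 1/54)) = 2.598, and power = Φ(2.598 − 1.960) = 73.8%, close to the stated value.

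Now treat each withdrawn rifampicin woman as wholly missing, which is the worst case because her earlier scores are kept. The shares are assumed.

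| Assumed share lost | Rifampicin n | Power |
|---|---|---|
| 0% | 54 | 73.8% |
| 5% | 51.3 | 72.7% |
| 10% | 48.6 | 71.5% |
| 20% | 43.2 | 68.8% |

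**4. Possible bias**

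Let w be the share of the rifampicin arm withdrawn and k the excess itch that these women would have shown over those who stay. Both are assumed. If they contributed no scores at all, the shift in the rifampicin mean is w × k:

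- 0.05 × 20 mm = 1.0 mm, which is 1/7 = 14% of the 7 mm planning difference (−16 against −23 mm) and 1/14 = 7% of the 14 mm one.
- 0.10 × 30 mm = 3.0 mm, which is 3/7 = 43% of 7 mm and 3/14 = 21% of 14 mm.
- Wider range: 0.02 × 14 mm = 0.3 mm to 0.20 × 30 mm = 6.0 mm.

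Each is an upper bound for its own inputs. If only half of a withdrawn woman's scores were lost (assumed), the first two become 0.5 × 1.0 = 0.5 mm and 0.5 × 3.0 = 1.5 mm.

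**The case against.** **The event may be rare.** The drugs named under Exclusion criteria are for HIV, hepatitis C and tuberculosis. Positive hepatitis C serology is itself an exclusion, and Drug interactions calls recruitment of women with active or treated tuberculosis most unlikely. Starting one of those drugs is not evidently linked to itch. This stands as a reason for caution about size. However, the list is introduced as non-exhaustive, the withdrawal rule has no closed list of its own, and the Background describes rifampicin as a potent enzyme inducer. Rarity is plausible but not established.

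**A reader might infer that the rifampicin arm loses nearly all its primary data, or that these women drop out of the analysis.** The article does not support this: scores up to withdrawal are included, and no exclusion from the analysis is stated. For the same reason, about 3 such women (5% of 54 = 2.7) would not simply use up that arm's 5% dropout allowance, since they contribute partial data.

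**A reader might infer that only one arm is affected.** UDCA-arm women given add-on rifampicin come under the rule too, and Current practice describes that addition as usual in severe disease where it is considered necessary.

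**A reader might infer a flat contradiction.** The withdrawal section says only that a woman need not necessarily leave, and its trigger is different. The intention-to-treat text governs the arm in which data are analysed, and retained data can meet it in part. Tension is the right word.

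**A reader might infer a bias towards rifampicin.** That holds only if the withdrawn women would have had worse itch, and nothing in the article shows this.

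**Conclusion.** The point holds as a design weakness of moderate weight, below the level of something that must be fixed before the trial can be relied on. What is certain from the text is that the event ends study participation, that no later itch scores are provided for, and that the trigger depends on being on rifampicin. Full intention-to-treat analysis of an outcome scored to delivery needs those scores.

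The effect on the result is not certain. Loss of power is slight: about 1 percentage point at 5% lost and about 2 at 10%, even counting each woman as fully missing. Any bias is of unknown size and direction. The 1 mm and 3 mm figures rest on assumed withdrawal shares and assumed excess itch, and overstate the effect for those inputs because earlier scores are retained. The case for acting is that scores not taken cannot be recovered, while taking them is cheap.

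**What to change.** Reconcile Concomitant medication, the Notes to Table 1, Withdrawal of participants and Data analysis so that starting an interacting medication does not end trial follow-up. State that scheduled itch scores, blood tests, adverse events and perinatal outcomes continue to be collected and are analysed in the allocated arm unless the woman withdraws consent. Settle in the same amendment the difference between mandatory withdrawal and a request to withdraw.

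The clinical handling of the study drug and of the interacting medication is left as the sponsor determines; no clinical rule is proposed here.

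The cost is a short amendment and a few more itch scores at visits that take place anyway.

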## Trial outcomes

### Primary outcome

Maternal pruritus score, measured as worst itch in the previous 24 h assessed on a patient-recorded visual analogue scale.

### Secondary outcomes

The secondary short-term maternal outcomes are defined as:
Serial biochemical indices of disease: serum concentration of bile acids (BA), bilirubin (total), alanine transaminase (ALT), gamma glutamyl transferase (GGT)Peak serum concentration (between randomisation and delivery) of BAMaximum doses of trial medications required, and days of such medicationsDays from randomisation to birthDays to resolution/amelioration of symptomsNeed for added treatment with UDCA or rifampicin as appropriate after 7 days of the randomly allocated drug therapyNeed for additional therapy at maximum trial dosage (e.g. antihistamines, cholestyramine, therapeutic plasma exchange/other)Incidence of gestational diabetes mellitus (WHO criteria) and its treatment (diet/metformin/insulin), and of gestational hypertension/pre-eclampsia (ISSHP criteria)Upper abdominal ultrasound/biliary pathologyMode of onset of labour, and gestation at onsetTiming of steroids (if any) for fetal pulmonary maturationDuration of labourPresence of meconium in the liquor intrapartumGestation at birthMode of birth, classified as spontaneous vaginal, instrumental vaginal or CaesareanReason for induction or pre-labour Caesarean sectionEstimated blood loss at birthTime for resolution of symptoms after birth

The secondary short-term perinatal outcomes are defined as:
Miscarriage (fetal death before 20^+ 0^ weeks gestation)Stillbirth (death before delivery ≥20^+ 0^ weeks gestation or > 400 g if gestation unknown)Neonatal death in hospital up to 7 days after birth (excluding death due to congenital anomalies)Neonatal unit admissions until infant discharge home from hospitalNumber of nights in each category of care (intensive, high dependency, special, transitional and normal) and total number of nights in hospitalBirth weight (g), and customised/population birth weight centile (GROW) [33]Apgar scores at 1 and 5 min after birthUmbilical arterial and venous pH (and base excess) at birthCord blood BANeed for supplementary oxygen prior to discharge, and number of days when such oxygen is requiredNeed for ventilation support (continuous positive airway pressure - CPAP/high flow/endotracheal ventilation)Pneumothorax (confirmed on chest X-ray)Need for phototherapyAbnormal cerebral ultrasound scanConfirmed sepsis (positive blood or cerebrospinal fluid cultures)Necrotising enterocolitis (Bell’s stage 2 and 3)Seizures (confirmed by EEG or requiring anticonvulsant therapy)Encephalopathy grade (worst at any time: mild, moderate, severe)Hypoglycaemia (blood glucose < 2.6 mmol/l on two or more occasions)Severe hypoglycaemia (blood glucose < 1.8 mmol/l on two or more occasions)Other indications and main diagnoses resulting in NNU admission.Mode of feeding at discharge from hospital

The primary outcome, maternal pruritus score, will be evaluated at 1 week after trial entry and then on a monthly basis up to 28^+ 0^ weeks gestation and then weekly to delivery.

The timepoints of evaluation of the secondary maternal outcomes are at 1 week post-randomisation visit, at monthly clinic visits at 20, 24 and 28 weeks gestation (if randomised prior to that), at weekly clinic visits after 28 weeks gestation and during admission for birth, and of the secondary neonatal outcomes at delivery and 1 week and 6 weeks after birth.

The following information post enrolment will be captured for health resource use:
Maternal: total number of nights (antenatal, intrapartum and postnatal) together with level of care including adult ICU.Infant: total number of nights for the baby in neonatal unit, together with level of care (e.g. neonatal ICU).

The costs of UDCA and rifampicin, together with the costs of any additional treatment, will be calculated in both the UDCA and rifampicin groups.

